## Abstract

**Background:**

Up to 30 % of children with acute asthma are refractory to initial therapy, and 84 % of this subpopulation needs hospitalization. Finding safe, noninvasive, and effective strategies to treat this high-risk group would substantially decrease hospitalizations, healthcare costs, and the psycho-social burden of the disease.

Whereas intravenous magnesium (Mg) is effective in severe refractory asthma, its use is sporadic due to safety concerns, with the main treatment goal being to prevent intensive care unit admission. In contrast, nebulized Mg is noninvasive, allows higher pulmonary drug concentrations, and has a much higher safety potential due to the lower rate of systemic delivery. Previous studies of inhaled Mg show disparate results due to the use of unknown/inefficient delivery methods and other methodological flaws.

**Methods/Design:**

The study is a randomized double-blind controlled trial in seven Canadian pediatric Emergency Departments (two-center pilot 2011 to 2014, Canada-wide November 2014 to December 2017). The trial will include 816 otherwise healthy children who are 2 to 17 years old, having had at least one previous wheezing episode, have received systemic corticosteroids, and have a Pediatric Respiratory Assessment Measure (PRAM) ≥ 5 points after three salbutamol and ipratropium treatments for a current acute asthma exacerbation. Eligible consenting children will receive three experimental treatments of nebulized salbutamol with either 600 mg of Mg sulfate or placebo 20 min apart, using an Aeroneb Go nebulizer, which has been shown to maximize pulmonary delivery while maintaining safety. The primary outcome is hospitalization within 24 h of the start of the experimental therapy for persistent respiratory distress or supplemental oxygen. Secondary outcomes include all-cause hospitalization within 24 h, PRAM, vital signs, number of bronchodilator treatments by 240 min, and the association between the difference in the primary outcome between the groups, age, gender, baseline PRAM, atopy, and “viral induced wheeze” phenotype (Fig. 1).

**Discussion:**

If effective, inhaled Mg may represent an effective strategy to minimize morbidity in pediatric refractory acute asthma. Unlike previous works, this trial targets nonresponders to optimized initial therapy who are the most likely to benefit from inhaled Mg. Future dissemination of results will include knowledge translation, incorporation into a Cochrane Review, presentation at scientific meetings, and a peer-reviewed publication.

**Trial registration:**

NCTO1429415, registered 2 September 2011.

**Electronic supplementary material:**

The online version of this article (doi:10.1186/s13063-015-1151-x) contains supplementary material, which is available to authorized users.

## Background

Acute asthma is a leading cause of pediatric emergency department (ED) visits and of pediatric hospitalizations [1], with the annual asthma expenditures in the United States exceeding $37 billion [2]. In 2005, 754,000 pediatric ED asthma visits were reported in the US [3, 4], and 27 % of these resulted in hospitalization [4]. Practice guidelines recommend high dose ß2 agonists, inhaled anticholinergics, and oral corticosteroids to manage major acute exacerbations [5–9]. However, this initial optimal therapy [9–11] is not always effective [12] because up to 30 % of patients with asthma are resistant to initial bronchodilation [13] in part due to ß2 adrenoreceptor gene polymorphism [14–32], and gene polymorphisms also impact the frequently delayed response to corticosteroids [33–35]. Finding further effective strategies to decrease pediatric asthma hospitalizations in this high-risk population is necessary.

Magnesium sulfate (Mg) produces rapid bronchodilation by multiple mechanisms [36–39] and can be given either intravenously (IV) or by nebulization. Two key meta-analyses of adult and pediatric trials have confirmed that the addition of IV Mg to routine therapy significantly decreases hospitalizations and improves lung function [40, 41]. These authors, as well as various asthma guidelines, recommend that IV Mg be considered in children not responding to initial management [40, 42–44]. However, IV Mg is used infrequently and often as a last resort [45, 46]. In contrast, the nebulization route is noninvasive and offers a major advantage of targeted delivery to the lower airway and less potential for side effects [47]. However, the benefit of nebulized Mg has not been well established.

The investigation of the efficacy of nebulized Mg has been limited, with disparate results. The dose of Mg varied seven-fold among studies [48–60], and only one study [48] limited participants to nonresponders to bronchodilators. Two meta-analyses of mainly adult studies have found a trend toward reduction in hospitalizations in patients given nebulized Mg [40, 61], with the recent Cochrane review reaching similar conclusions [59]. The main limitations of past pediatric studies are failure to limit participants to nonresponders to bronchodilators, inadequate use of anticholinergics, use of inefficient delivery methods, and small sample size [49, 58, 60, 62]. In contrast, this study focuses on the poor responders to optimized baseline acute asthma therapy. This group is at the highest risk of hospitalization and the most likely to benefit from nebulized Mg intervention. Furthermore, previous studies have used nebulizers of suboptimal/unknown efficacy. In contrast, the device used in this study has been pre-tested and shown to deliver a considerably greater proportion of the drug into the lungs compared to the conventional nebulizers.

### Research questions and study hypothesis

#### Primary question

The primary question is whether, in children 2–17 years of age with acute asthma who have persistent moderate to severe airway obstruction despite maximized initial bronchodilator and steroid therapy, a reduction can be achieved in the probability of hospitalization within 24 h of starting experimental therapy. Specifically, this trial compares those patients who receive three nebulized Mg and salbutamol treatments to those receiving only nebulized salbutamol.

#### Secondary questions

The trial seeks to determine the following for these treatment modalities:Is there a difference in the probability of all-cause hospitalization within 24 h of starting therapy?Is there a difference in the changes in the validated Pediatric Respiratory Assessment Measure (PRAM), respiratory rate, oxygen saturation, and blood pressure to 240 min?Does the treatment effect with respect to primary outcome vary among the subgroups defined by the following variables: age, sex, pre-randomization PRAM score, personal history of atopy and “viral-induced wheeze” phenotype?

#### Hypothesis

We hypothesize that the children with PRAM ≥5 points after optimized initial inhaled bronchodilator and systemic steroid therapy who are given nebulized Mg in addition to nebulized salbutamol will have a significantly lower probability of hospitalization compared to those given salbutamol only.

## Methods/Design

### Study design and population

This is a seven-center, randomized, double-blind controlled trial. Two study groups are compared: nebulized salbutamol with Mg sulfate and nebulized salbutamol with placebo. This study has received approval by the Research Ethics Board of the Hospital for Sick Children. Furthermore, local Research Ethics Boards have approved the study at all participating sites (see Additional file 1). A written informed consent and assent where appropriate is being obtained from all study participants.

All otherwise healthy children 2–17 years of age with a past history of asthma/recurrent wheeze arriving in the ED when the study nurses are on duty with a presenting PRAM ≥5 are considered potentially eligible. Following assessment by the ED physician, the patients receive oral/IV corticosteroid plus three salbutamol and ipratropium inhalations according to the local management guidelines [63–68]. If the PRAM is still ≥5 after the initial therapy, the study nurse confirms eligibility, measures the pre-randomization PRAM score, and obtains informed consent.

#### PRAM score

PRAM is a validated 12-point clinical asthma severity score [69], exhibits the most comprehensive measurement properties of all asthma scores [70], and has been successfully used as an outcome in major trials [71]. It is the only score with demonstrated criterion validity, using respiratory resistance as the gold standard [72]. PRAM has been validated in both preschool and school-aged children who have been assessed in the ED for asthma and has a strong association with admission [73]. The score has inter-rater reliability consistently above 70 % [73] and is currently implemented in virtually all pediatric EDs across Canada. Children with PRAM ≥5 following initial bronchodilator therapy have at least a 30 % probability of hospitalization and represent 84 % of all acute asthma admissions in children. All participating EDs now measure the PRAM score as part of routine clinical assessment in their EDs in children with acute asthma. Because Calgary is situated 1000 m above sea level, oxygen saturations there can be expected to be approximately 2 % lower than in Toronto (International Civil Aviation Organization, Manual of the ICAO Standard Atmosphere, Doc 7488-CD, Third Edition, 1993, ISBN 92-9194-004-6). Therefore, the oxygen saturation component of the PRAM is adjusted in Calgary.

#### Inclusion criteria

Inclusion criteria are (1) 2 to 17 years of age, (2) diagnosis of asthma/reactive airways/viral-induced wheeze plus at least one prior acute episode of wheezing treated with inhaled ß2 agonists or oral corticosteroids, (3) persistent moderate to severe airway obstruction after oral steroid and three doses of salbutamol and ipratropium, defined as a PRAM ≥5 [73].

#### Exclusion criteria

Exclusion criteria are (1) no past history of wheezing or bronchodilator therapy; (2) prior IV Mg therapy during the index visit; (3) critically ill children requiring immediate intubation; (4) coexistent renal, chronic pulmonary, neurologic, cardiac, or systemic disease; (5) children who in the opinion of the treating physician require a chest radiograph due to atypical clinical presentation and are diagnosed to have lobar consolidation with pneumonia, felt to be the primary cause of respiratory distress; (6) known hypersensitivity to Mg sulfate; (7) patients previously enrolled; (8) insufficient command of the English or French language; and (9) lack of a phone.

#### Delivery device

To ensure adequate delivery of the experimental treatment into the lungs, we have pre-tested the Aeroneb™ Go Micropump Nebulizer along with the Idehaler™ Pocket system without valves that connects with a facemask in vitro and in vivo. We found that this device deposited 20 % of the charge dose compared to 4 % by conventional nebulizers, while also maintaining acceptable osmolarity and safety [74]. This device has been distributed to all participating sites, related training provided, and Health Canada approval obtained. All experimental treatments are delivered with this device. This device is fully licensed both in the United States and in Europe and is currently awaiting license approval in Canada. We do not anticipate any difficulties with its official adoption by the time this trial is concluded.

### Sample selection

Children presenting to the collaborating EDs at The Hospital for Sick Children, Children’s Hospital of Eastern Ontario, Ste Justine’s Hospital, Alberta Children’s Hospital, Stollery Hospital, Children’s Hospital of Winnipeg and the B.C. Children’s Hospital who meet eligibility criteria are approached for enrollment when the research nurses are on duty. The research nurses keep a log of all children presenting to the ED with acute asthma during the study period whether randomized or not in order to assess the generalizability of the study. All aforementioned hospitals are tertiary care centers, which see the entire clinical and demographic spectrum of the asthma population.

### Pre-study screening and baseline evaluation

All previously healthy children 2 and 17 years of age with acute asthma have a PRAM score measured in triage. Those meeting local ED criteria for enhanced therapy receive either oral dexamethasone, oral prednisolone/prednisone, or IV hydrocortisone plus three salbutamol and ipratropium inhalations via a Metered Dose Inhaler/Valved Holding Chamber (MDI/VHC)/nebulizer according to the local asthma pathway and 20 min apart.

### Study procedures

At the conclusion of the three baseline inhalations, the research nurse assesses eligibility and measures the pre-randomization PRAM score. Eligible children with PRAM ≥5 are approached, and informed consent is obtained. Subjects are randomly allocated to receive three consecutive nebulizations of salbutamol with either diluted Mg sulfate or diluted 5.5 % saline placebo 20 min apart [48] using the Aeroneb™ Go Micropump Nebulizer along with the Idehaler™ Pocket system. Specifically, each treatment utilizes 600 mg (1.2 mL) of Mg sulfate or 1.2 mL 5.5 % saline, 5 mg (1 mL) of salbutamol, and 3.8 mL of sterile water (Fig. 1).

**Fig. 1 Fig1:**
[figure not shown]
Flow diagram of participant study flow. The intervention consists of two treatment arms with solutions of identical osmolarity consisting of inhaled salbutamol with Mg sulfate (experimental arm) and with equivalent saline placebo (control arm). The primary outcome is hospitalization to inpatient unit for asthma-related symptoms within 24 h of randomization. **PRAM* Pediatric Respiratory Assessment, ***Mg* magnesium

### Randomization and masking

The Research Coordinating Pharmacist at SickKids produced Master Randomization tables, stratified by site and age (≥6 years versus less), using a permuted block randomization of six and eight in a 1:1 ratio of active Mg sulfate to placebo, using random number generating software. The Master Randomization tables are held at the site Research Pharmacies. Consecutively numbered kits are prepared by each pharmacy according to the step-by-step procedure manual provided by Research Coordinating Pharmacist at SickKids. Upon receiving the informed consent, the study nurse obtains the next appropriate numbered study kit from the locked research fridge in the ED (Mg has to be refrigerated) and enters the number in the confidential logbook. Since Mg sulfate solution is hypertonic, 5.5 % saline was chosen as a placebo. Using sterile water as a top-up diluent in both arms produces solutions of identical isotonicity 380 mOsm/L in both study groups. Because the deposition of inhaled drugs is weight-independent [64], a uniform Mg dose is used in all children.

The patients, research nurses and ED physicians are blinded to the treatment assignment. Only the pharmacies are unblinded. Each site is given detailed requirements for drug accountability and handling to ensure compliance with Health Canada regulations. The active Mg and placebo hypertonic saline mixture with salbutamol and sterile water are very similar in volume, color, taste, and smell when nebulized (tested in the research pharmacy at SickKids). To assess blinding, the research nurse and parents are asked at the conclusion of the experimental therapy which intervention they think the child had received.

In case of increasing respiratory distress, IV Mg may be given after the experimental therapy, provided the patient is not hypotensive. In the unlikely event that the patient develops hypotension requiring therapy or apnea and the ED physician feels that the experimental therapy cannot be safely continued, further doses of the experimental treatment are stopped. If these Mg side effects are also accompanied by severe distress and additional IV Mg is warranted, the code may be broken for that patient. Unblinding will only occur if the clinical treatment of the patient will change because the physician knows which arm of the study the patient was previously enrolled. The study PI/local PI and the study nurses will remain blinded. No patients participating in our inhaled Mg study received experimental therapy unblinded.

The study nurses also keep continuous study logs with the characteristics and outcome of the participating and nonparticipating eligible acute asthmatics ≥2 years of age; these logs will also be used to track missed patients, those excluded for criteria, and patients who refused participation, which will help document any selection bias.

### After the intervention

Following the study medication, the patients continue to receive further salbutamol as frequently as clinically warranted as per the treating ED physician. Disposition is also determined by blinded ED physicians. Discharged patients receive a prescription for inhaled salbutamol every 4 h as necessary for the next week and daily oral corticosteroid according to local practice. All participating families receive instructions to visit their primary care provider/ED if salbutamol has to be given more often than every 4 h for increased work of breathing/severe cough and if the respiratory status interferes with usual play/normal speech or activity.

### Outcome measures

#### Primary outcome measure

The primary outcome measure is hospitalization (based on the ED physician’s decision to admit) to an inpatient unit within 24 h of the start of the experimental therapy for persistent respiratory distress or for supplemental oxygen. Children deemed to be admitted but who due to lack of bed availability are never transferred to the ward will be analyzed as hospitalized. Extended ED stays without a decision to admit are not considered admitted.

#### Secondary outcome measures

The two groups will also be compared with respect to the following:All cause hospitalization rate by 24 h to examine Mg impact on side effects, such as hypotension necessitating admission.Changes in the PRAM, respiratory rate, and oxygen saturation from the start of the first experimental nebulization to 60, 120, 180, and 240 min and the changes in the blood pressure from the first experimental nebulization to 20, 40, 60, 120, 180, and 240 min.Number of salbutamol treatments within 240 min of starting study medication.An association between hospitalization and age, sex, symptom duration <24 h [60], pre-randomization PRAM score, personal history of atopy, and “acute viral induced wheeze” phenotype [75–81].

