### Sample size

The sample size calculation is based on the targeted minimal significant between-group difference in proportions of hospitalizations of 10 %, which has previously been shown to impact treatment decisions. The estimated probability of hospitalization is based on our fully blinded pilot data (pilot patients form an integral part of this trial), where the overall hospitalization rate is close to 50 %. This is a superiority study in which the adoption of the Mg therapy can only be recommended for future practice if the probability of the primary outcome in the Mg group is significantly lower than in the placebo group. With 408 patients per arm (816 in total), a two-sided test with a type I error of 0.05 will have 80 % power to achieve statistical significance if Mg therapy reduces the probability of hospitalization from 50 to 40 % (that is, absolute reduction of 10 %) [82].

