#### Secondary analysis

Secondary analysis will include the following:A Fisher’s exact test to compare the rates of all cause admissions in the two arms.A repeated measures ANOVA to compare treatment arms with respect to the PRAM score, respiratory rate, heart rate, oxygen saturation, and blood pressure over time. Baseline values will be added to the model as a covariate.A Poisson model will be used to compare the number of salbutamol treatments used in the ED in the regression analysis of the two study arms, including interaction terms with the treatment group, which will be used to examine the subgroup effects with respect to the primary outcome. The following variables will be used to define subgroups: age, sex, pre-randomization PRAM score, and personal history of atopy. The statistical tests of hypotheses for the secondary outcomes a) through d) will be two-sided at the 0.00625 level to account for the issue of multiple testing and to maintain an overall type 1 error of 0.05.

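### All-cause hospitalization is assigned to examine magnesium side effects, but as a single proportion containing the primary outcome it measures net effect and cannot serve as the side-effect test

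*Protocol article*

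**What the plan says.** All references are to the protocol article.

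- **Secondary outcome measures** gives the all-cause outcome its purpose: "All cause hospitalization rate by 24 h to examine Mg impact on side effects, such as hypotension necessitating admission".
- **Secondary analysis** fixes the test: "A Fisher’s exact test to compare the rates of all cause admissions in the two arms". Tests of the secondary outcomes "will be two-sided at the 0.00625 level to account for the issue of multiple testing".
- **Primary outcome measure** counts hospitalization "within 24 h of the start of the experimental therapy for persistent respiratory distress or for supplemental oxygen". Every primary event is therefore also an all-cause event in the same 24 h window.
- **Sample size** refers to blinded pilot data "where the overall hospitalization rate is close to 50" %, and plans on a reduction from 50 % to 40 %.
- **Secondary questions** asks about all-cause hospitalization neutrally, without mentioning side effects.
- **Other outcomes** and **Safety** track hypotension, apnea and ICU admission. Blood pressure changes to 240 min are compared between arms. The monitoring committee is told of all serious adverse events within 48 h.

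**The concern.** The purpose and the test do not fit each other. The purpose is to find out whether magnesium causes admissions through side effects. The test compares a total in which respiratory admissions are expected to be a large part, and the trial hopes magnesium will lower that part. A beneficial effect on respiratory admissions and a harmful effect through side effects move the total in opposite directions, so the test shows only their difference. If there is no respiratory effect, a small excess must still be detected against the sampling variation of a proportion near one half, where that variation is greatest.

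What is at stake is interpretation. If the result is read for its stated purpose, a neutral or favourable all-cause comparison could be taken as evidence that magnesium does not cause side-effect admissions, which it would not be.

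**Working it through.** **Inputs from the article:** 408 per arm; planned rates 50 % and 40 %; two-sided 0.05 for the primary outcome; two-sided 0.00625 for secondary outcomes; Fisher's exact test.

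**Assumption, not in the article:** no side-effect admissions on placebo, and an absolute excess *s* on magnesium of 1 to 5 points of the whole arm. All-cause admission on placebo is set to 50 %, and on magnesium to its respiratory rate plus *s*.

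**Step 1: reproduce the planned sample size.** With p1 = 0.50, p2 = 0.40 and mean 0.45:

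m = [1.960 × √(2 × 0.45 × 0.55) + 0.842 × √(0.50 × 0.50 + 0.40 × 0.60)]² / 0.10² = 387.3, so 388 per arm.

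With continuity correction: n = (m/4) × [1 + √(1 + 4/(m × 0.10))]² = 407.1, so 408 per arm.

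The stated figure is reproduced. Exact Fisher power at 408 per arm is 80.8 %.

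**Step 2: break-even point.** At the planned effect, the all-cause rate on magnesium is 40 % + *s*. It stays below 50 % until *s* exceeds 10 points, and 0.10 × 408 is about 41 children.

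**Step 3: behaviour of the planned all-cause test.** Exact enumeration of the two-sided Fisher test, 408 per arm, level 0.00625:

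| Excess *s* (expected magnesium children) | Planned effect (40 % vs 50 %): significant for magnesium | Planned effect: significant harm | No respiratory effect (50 % vs 50 %): significant harm |
|---|---|---|---|
| 1 point (4) | 42 % | about 0 | 0.6 % |
| 2 points (8) | 31 % | about 0 | 1.3 % |
| 3 points (12) | 22 % | about 0 | 2.6 % |
| 5 points (20) | 9 % | about 0 | 8.6 % |

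With half the planned effect (45 % vs 50 %), a 5-point excess makes the two rates equal, and the chance of showing harm is 0.2 %.

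**Step 4: compare non-respiratory admissions on their own.** For *k* of 408 against 0 of 408, Fisher's p is 0.0075 at *k* = 8 and 0.0037 at *k* = 9, so nine events are needed at 0.00625. Six are needed at 0.05 (p = 0.031; *k* = 5 gives 0.062). Power is the binomial probability of reaching that count:

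| Excess *s* | Power at 0.00625 | Power at 0.05 |
|---|---|---|
| 1 point | 2 % | 23 % |
| 2 points | 43 % | 83 % |
| 3 points | 86 % | 98 % |
| 5 points | 99.9 % | about 100 % |

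**Step 5: one worked case.** Take 163 respiratory admissions on magnesium (40 % of 408) and 204 on placebo (50 %), with 20 side-effect admissions against 0. Compared alone, 20 vs 0 gives p = 0.0000015. Within the all-cause total, 163 + 20 = 183 against 204 gives p = 0.16, with the direction favouring magnesium.

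**The case against.** **Safety does not rest on this test.** This stands. Blood pressure, the direct measure of the side effect named, is compared by arm at six time points. Hypotension, apnea and ICU admission are tracked and count as serious adverse events that go to the monitoring committee. A reader might infer that a side-effect excess would go unseen in the trial, or that side effects cannot be assessed at all; the article does not support that.

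**The count can be recovered.** This also stands. The primary outcome is nested in the all-cause outcome, with the same arms and window, so non-respiratory admissions are all-cause minus primary. But the article names no comparison of that difference; it names the all-cause test for the side-effect purpose.

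**All-cause hospitalization is a legitimate companion to a cause-specific primary outcome.** Agreed, and Secondary questions presents it that way. Only the purpose attached to it under Secondary outcome measures is at fault.

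**Large excesses are not likely.** Partly stands. The article reports no hypotension or apnea, with 207 enrolled. If about 103 of these received magnesium (an assumption), the one-sided 95 % upper bound is 1 − 0.05^(1/103) = 2.9 % for those two events, and admissions caused by them are a subset. The 5-point row is thus the far end of the range. At the low end the direct comparison is weak too: 4 vs 0 gives p = 0.12 and 5 vs 0 gives p = 0.06.

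**The article is condensed and the analysis plan is not shown.** Further safety tables may well exist there. The point does not depend on their absence, because the article itself states the outcome, its purpose, the test and the level, and these do not match.

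**Conclusion.** The point holds as a mismatch between a stated purpose and a stated test. All-cause hospitalization is a net-effect outcome. For an assumed 1 to 5 point excess of side-effect admissions on magnesium and none on placebo, the planned test has about 0 chance of showing harm at the planned effect and 0.6 % to 8.6 % with no respiratory effect. A direct comparison has 2 % to 99.9 % over the same range, so the gain is real from about 2 points upward and negligible at 1 point.

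It is tempting to add that almost all all-cause admissions are respiratory. The article gives no split by cause, so that is only an inference from the overall rate and the absence of hypotension and apnea. The calculations need only that the primary outcome is contained in the total, plus the stated assumptions. Given the other safety measures, this is an inexpensive improvement to one secondary outcome and not a gap in the trial's safety monitoring.

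**What to change.** 1. Under Secondary outcome measures, describe all-cause hospitalization as a net-effect outcome and a sensitivity check on how the cause of admission was classified, and remove the side-effect purpose.
2. There and under Secondary analysis, add a by-arm comparison of hospitalization within 24 h for reasons other than respiratory distress or oxygen, with counts, Fisher's exact test and an exact confidence interval for the difference.
3. Read it beside the by-arm counts of hypotension and apnea.

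**Cost:** a wording change and one table. The reason for admission is already needed to classify the primary outcome, and the sample size is unaffected. No extra report to the monitoring committee is needed, since serious adverse events already reach it.

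**Downsides:** with very few events (an excess near 1 %) power is low and the interval is wide relative to the rate. A child admitted for both a side effect and respiratory distress is counted as respiratory, so the new outcome can miss some side-effect admissions. That is why step 3 matters.
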